## Abstract

**Background:**

Recent research has shown that wearing multifocal glasses increases the risk of trips and falls in older people. The aim of this study is to determine whether the provision of single-lens distance glasses to older multifocal glasses wearers, with recommendations for wearing them for walking and outdoor activities, can prevent falls. We will also measure the effect of the intervention on health status, lifestyle activities and fear of falling, as well as the extent of adherence to the program.

**Methods/Design:**

Approximately 580 older people who are regular wearers of multifocal glasses people will be recruited. Participants will be randomly allocated to either an intervention group (provision of single lens glasses, with counselling and advice about appropriate use) or a control group (usual care). The primary outcome measure will be falls (measured with 13 monthly calendars). Secondary measures will be quality of life, falls efficacy, physical activity levels and adverse events.

**Discussions:**

The study will determine the impact of providing single-lens glasses, with advice about appropriate use, on preventing falls in older regular wearers of multifocal glasses. This pragmatic intervention, if found to be effective, will guide practitioners with regard to recommending appropriate glasses for minimising the risk of falls in older people.

**Trial Registration:**

The protocol for this study was registered with the Clinical Trials.gov Protocol Registration System on June 7^th ^2006 (#350855).

## Background

Refractive error due to presbyopia is the most prevalent form of visual impairment in older people [1]. Presbyopia is a visual condition in which the crystalline lens of the eye loses its flexibility, making focusing on close objects difficult [2]. To correct for presbyopia, older people are either prescribed separate single lens glasses for distant and near vision, or for convenience, a single pair of multifocal (bifocal, trifocal or progressive lens) glasses. Multifocal glasses have specific benefits for tasks that require changes in focal length, including everyday tasks of driving, shopping and cooking. However, multifocal glasses also have certain disadvantages as outlined below.

Bifocal glasses have optical defects, such as prismatic jump at the top of the reading segment, which causes an apparent displacement of fixed objects [2,3]. The lower lenses of all types of multifocal glasses blur distant objects in the lower visual field and this factor, in particular, may represent a significant problem for older people [3,4]. Multifocal glasses have been shown to impair distant depth perception and contrast sensitivity [5] and two recent studies have found that multifocal glasses impair step negotiation and the accuracy of foot placement when stepping onto a raised surface in older people [6,7]. These studies reported that when wearing multifocal glasses versus single-lens glasses, older people displayed more variability in minimum vertical toe clearance when stepping up [7] and in foot placement (lead or trail toe-to-platform distance) when negotiating a raised surface [6]. Contacts with the raised platform's edge [7] and trips [6] only occurred in the multifocal glasses conditions.

Other studies have reported significant associations between wearing multifocal glasses and tripping incidents [8,9] and a prospective study of 156 older people found that multifocal glasses wearers were significantly more likely to fall during 12 months of follow-up, after adjusting for age and known physiological risk factors for falls [5]. Findings from this study also indicated that multifocal glasses wearers were more likely to fall when outside their homes, and when walking up or down stairs. The population attributable risks of regular multifocal glasses use were 35% for any falls and 41% for falls outside the home.

To date, there is no evidence that falls can be prevented by restricting the use of multifocal glasses. To address this need we are conducting the Visual Intervention Strategy Incorporating Bifocal & Long-distance Eyewear (VISIBLE) study. The primary aim of this randomized controlled trial is to determine whether the provision of supplementary single-lens distance glasses to elderly multifocal glasses wearers, together with recommendations for wearing them for standing and outdoor activities, can reduce falling rates over a 13-month period. Secondary aims include determining whether, as a result of fewer falls, the intervention has beneficial effects for physical and emotional wellbeing, falls efficacy and activity levels, and whether a range of physical, psychological and socio-demographic factors can predict compliance in the intervention group.

## Methods

### Participants

Participants will be recruited from the following sources: sampling of older people from the electoral roll in northern Sydney, residents of retirement (self-care apartment) villages in the Central Coast, Blue Mountains and Illawarra regions of New South Wales, outpatients and inpatients discharged from rehabilitation and orthopaedic wards at hospitals within northern and eastern Sydney, and responders to newspaper advertisements and media coverage.

Eligibility will be assessed primarily with a telephone screening questionnaire. Participants will be eligible for the trial if they are at a relatively high risk of falls defined as (a) aged 65–79 years with a Timed Up and Go Test (TUG) of 15+ seconds [10] and/or a history of one or more falls in the last 12 months or b) aged 80 years and over. Other inclusion criteria comprise: a user of bifocal, trifocal or progressive-lens glasses 3+ times/week when walking outdoors; having had a review by an optometrist or ophthalmologist in the last 12 months; not currently using single-lens distance glasses; and indicating that they are at least 'quite confident' of complying with the study recommendations.

People will be ineligible if they: reside in a high-care residential facility, have a cognitive impairment (a Mini-Mental State Examination (MMSE) [11] score of less than 24), a severe visual impairment (Melbourne Edge Test score of <16 dB) [12], insufficient English language skills to understand the assessment and/or intervention procedures, have planned ophthalmic surgery in the next 12 months, or have an unstable medical condition at enrolment.

The University of New South Wales Human Research Ethics Committee (HREC) approved the study protocol (HREC Number 04229) as have ethics committees at the participating hospitals. The participant flow diagram is presented as figure 1 (Figure 1).

**Figure 1 F1:**
[figure not shown]
**Flow of participants through the trial**.

### Initial Assessment

Initially the study aims will be explained, and then the participants will be asked if they feel confident that they could manage and wear two pairs of glasses if randomised to the intervention. Only participants who answer 'very or quite confident', as opposed to 'not confident' or 'very unconfident', will undergo consent, assessments and randomisation. The approach of targeting the intervention to those who consider it to be reasonable and manageable is based on strong evidence from hip protector trials [13].

Demographic details and potential confounders will be recorded, including age, gender, living alone status, MMSE [10], number of falls in past year, number and type of medications, physical activity levels, gait aids, medical conditions relevant to falls (e.g. arthritis, syncope, diabetes and depression), current glasses use and ocular history. Baseline lifestyle activities (using the Adelaide Activities Profile (AAP)) [14], health status (SF-12) [15], and falls efficacy (Falls Efficacy Scale – International (FES-I scale) [16] will be measured.

The following vision and physical assessments will then be carried out. Corrected and uncorrected uniocular and binocular visual acuity will be assessed using a 3-metre logMAR chart [17]. Falls risk will be measured with the short-form Physiological Profile Assessment (PPA) [18] which includes five validated measures of physiological falls risk (visual contrast sensitivity, postural sway, quadriceps strength, reaction time and lower limb proprioception). In multivariate models these variables provide an overall falls risk score, and can predict those at risk of falling with 75% accuracy in community and retirement village settings. Functional mobility will be assessed with the TUG test [10], and the sit-to-stand test [19].

### Randomisation

After completion of the initial assessment, participants will be formally entered into the study and randomised to intervention or control groups. Participants will be stratified by assessment site (Greenwich or Prince of Wales Hospitals) and recruitment source (hospital or community contact).

Then each stratum will be randomly allocated in permuted blocks of 10 using sequentially-numbered opaque envelopes containing group assignment.

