**Figure 3 F3:**
[figure not shown]
**Simulated view of street scene as viewed through single-lens distance (panel A) and bifocal glasses (panel B)**. The footpath misalignment (a commonly reported environmental factor involved in outdoor falls) is clearly seen in panel A, but blurred in panel B.

The optometrist/counsellor will then instruct participants to use their new single-lens glasses for most walking and standing activities, and in particular when undertaking the following activities: walking up or down stairs outside the home, walking in the street and at shopping centres, walking or standing in other people's homes and unfamiliar buildings, negotiating rough or uneven ground and getting off and on public transport. Multifocal glasses use will not be discouraged for seated tasks, especially those that require frequent changes in focal length such as driving, and indoor standing and walking tasks that require changes in focal depth where there is minimal risk (e.g. cooking and selecting items in the supermarket).

To assist with the swapping of glasses, participants will be provided with a "glasses cord" for wearing around the neck and/or a hard or cloth glasses holder for keeping the second pair of glasses in a pocket. Intervention group participants will also be provided with a booklet reinforcing the advice. Table 1 outlines the strategies that will used to maximise compliance throughout the trial (Table 1). Any perceived barriers to compliance will be recorded.

**Table 1 T1:** Strategies to be used to maximise compliance

1	A strong evidence-based rationale for the intervention and clear recommendations will be provided.
2	The mechanism by which multifocal glasses can predispose to falls will be demonstrated during counselling using the example of the most commonly reported environmental factor involved in outdoor falls (Figure 2).

3	New glasses will be provided at no cost.

4	Perceived barriers to using two pairs of glasses will be identified and discussed during counselling.

5	An information brochure with recommendations and illustrations on appropriate use of glasses will be provided.

6	A hard/soft case glasses holder (to be worn around the neck and/or placed in the participant's pocket) to aid the swapping of glasses will be provided.

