7	Second counselling sessions delivered over the phone or at home visits will address perceived barriers to use of glasses for participants with inadequate compliance, i.e. "never/occasionally" complying with the recommendations.

8	Written reminder cards will be provided with falls diaries and prompts will be made during follow-up telephone calls.

Participants in the control group will also have the same optometric examination as participants in the intervention group. For the estimated 80% of participants who will not need a change of prescription (n = 234), no new glasses will be prescribed. For the expected 20% who will require a prescription change (n = 56), updated multifocal lenses will be prescribed according to the above criteria and fitted at a second visit. Control group participants will be given no specific advice regarding the use of their glasses.

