### Sample size calculation

Approximately 580 participants (290 per group) will be recruited. The study will have 80% power to detect as significant at the 5% level a 23% reduction in the rate of falling (i.e. an IRR of 0.77 using negative binomial regression analysis) in the 13-month follow-up period. This represents a reduction from 0.85 falls/person (an established rate of falling in a high-risk control group equivalent to our sample) [22,23] to 0.65 falls/person in the intervention group. This allows for an 8% loss to follow-up defined as withdrawing from the study and/or not completing the falls diaries, 70% compliance in the intervention participants and a rate of 0.57 falls/person among those complying with the intervention

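### A single published block size of 10 in each of four strata makes up to about one allocation in six predictable to anyone who knows the earlier ones; randomly varied sizes would avoid this cheaply

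*Protocol article*

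**What the plan says.** The Randomisation section of the protocol article defines the strata: "Participants will be stratified by assessment site (Greenwich or Prince of Wales Hospitals) and recruitment source (hospital or community contact". Two sites by two sources gives four separate sequences, two per site. The allocation method follows: "Then each stratum will be randomly allocated in permuted blocks of 10 using sequentially-numbered opaque envelopes containing group assignment". No variation in block size is mentioned.

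Allocation comes after baseline: "After completion of the initial assessment, participants will be formally entered into the study and randomised to intervention or control groups". The Sample size calculation section gives the total and the split: "Approximately 580 participants (290 per group) will be recruited".

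The Initial Assessment section places a self-rated screen before consent, in which "the participants will be asked if they feel confident that they could manage and wear two pairs of glasses if randomised to the intervention". The consequence is that "Only participants who answer 'very or quite confident', as opposed to 'not confident' or 'very unconfident', will undergo consent, assessments and randomisation".

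The Intervention section shows that the arms are handled differently in the open. In one arm, "The optometrist/counsellor will then instruct participants to use their new single-lens glasses for most walking and standing activities"; in the other, "Control group participants will be given no specific advice regarding the use of their glasses". The primary outcome section keeps three staff functions unaware of allocation: receiving falls calendars, making follow-up calls and entering data. The article describes no masking of participants or of the optometrist/counsellor, and the intervention does not allow it.

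**The concern.** Opaque envelopes hide the next assignment, but they do not hide past ones. With a constant, known block size, past assignments carry information about the next. Once one arm has used its places in a block, every remaining place is certain, and the last place of every block is always certain.

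At stake is selection at entry. A person who expects a particular arm next could bring forward or delay a candidate, or lean one way on a borderline eligibility decision. The exclusion for an unstable medical condition, for example, comes with no stated criterion in the article. The confidence screen concerns willingness to follow one arm's advice, so entry timed around it could make the arms differ in motivation. Falls are recorded by participants who know their arm, so motivation could affect reporting as well as adherence.

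**Working it through.** **Inputs.** Block size 10 and four strata (Randomisation); 580 participants, 290 per group (Sample size calculation). A 5:5 split within each block is inferred from the equal groups. The article states no predictability figure, so there is none to reproduce.

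**Certain allocations per block.** A 5:5 block of 10 has C(10,5) = 252 equally likely orderings. The certain allocations are the final run of identical assignments. A final run of exactly *k* occurs in 2 × C(9−k, 4) orderings:

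| Run length *k* | Orderings | Share of 252 |
|---|---|---|
| 1 | 140 | 55.6% |
| 2 | 70 | 27.8% |
| 3 | 30 | 11.9% |
| 4 | 10 | 4.0% |
| 5 | 2 | 0.8% |

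Mean = (140×1 + 70×2 + 30×3 + 10×4 + 2×5)/252 = 420/252 = 1.667 per block, or 16.7%. The closed form 2m/(m+1) with m = 5 gives the same: 10/6 = 1.667.

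**Across the trial.** With complete blocks, 58 × 1.667 = 96.7 of 580. Simulating 580 participants over four strata with incomplete last blocks gives 16.3%, and 0.163 × 580 ≈ 95.

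**Best guess.** Always guessing the arm with more places left, and tossing a coin when the arms are level, gives an expected number correct per block of m + (2^(2m)/C(2m,m) − 1)/2 = 5 + (1024/252 − 1)/2 = 6.53, or 65.3% against 50% by chance. That figure includes the certain places. For the others it is (6.53 − 1.67)/(10 − 1.67) = 4.86/8.33 ≈ 58%.

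**Other fixed sizes, for scale.** The certain share is 1/(m+1): 33.3% for blocks of 4, 25% for 6, 20% for 8 and 14.3% for 12.

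**Randomly varied sizes.** These were simulated over four strata with 580 participants. The tracker knows the set of sizes and every earlier allocation, but not the order of the sizes.

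| Scheme | Certain | Best guess correct |
|---|---|---|
| Fixed 10 | about 16% | about 65% |
| 8, 10, 12 | about 1.2% | about 65% |
| 6, 8, 10 | about 1.5–1.7% | about 66% |
| 4, 6, 8 | about 2.4–2.5% | about 68% |

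Varying the sizes removes nearly all certainty but hardly changes the best-guess rate. Smaller sizes make that rate worse.

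**The case against.** The strongest reply is that the figures need a tracker, and the article does not put one at the point of enrolment. It does not say who holds or opens the envelopes, or that those who screen and enrol learn earlier allocations. An article commonly leaves custody of envelopes and separation of roles to the full protocol. This stands. A reader might infer that enrolling staff see each allocation, but the text does not support that as fact, and silence on custody is not a fault here.

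Several further points also stand:

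- Fitting and counselling come at a second visit about four weeks after the initial assessment. Controls have the same optometric examination, and the expected 20% of them with a prescription change are also fitted at a second visit. Treatment contact therefore reveals the arm late, and a second fitting alone does not separate the arms. An immediate, complete count needs sight of the envelope contents or the prescription.
- The confidence answer is the participant's own, on four named levels. Most eligibility criteria are concrete, and allocation already follows baseline assessment. What remains open is mainly the timing of entry and borderline eligibility.
- Many baseline risk factors are recorded and the Statistical analysis section allows adjustment, so an imbalance in measured falls risk could be partly corrected. It would be too strong to say that analysis could do nothing. Differences in motivation above the confidence threshold are less well covered.
- Ten is a fairly large block, and smaller fixed blocks would be more predictable.

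None of this gives a reason to keep the size constant and in print. The block size is a stated design choice, not a detail left to another document, and a better choice is available at little cost.

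**Conclusion.** The point holds as an avoidable weakness in a stated choice, of minor to moderate priority. Under full knowledge of earlier allocations in a stratum, knowledge of the block size and 5:5 blocks, about one allocation in six is certain (1.67 per block) and about 65% can be guessed correctly overall. The figure of about 95 of 580 is a ceiling, because it needs all four sequences to be tracked in full.

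These numbers measure predictability, not bias. A reader might conclude that allocation was subverted or that the falls rate ratio is biased. Nothing in the article shows either, and no effect on the rate ratio has been estimated or bounded.

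**What to change.** For the envelopes not yet used, generate new lists with block sizes that vary at random around the present one, for example 8, 10 and 12. Do not disclose the sizes or their set to recruiting staff, and keep the four strata. Finish the block in progress in each stratum before the new list starts, so that balance already achieved is not lost. Do not move to smaller blocks, since that raises the best-guess rate.

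The gain is a drop in certain allocations from about 16% to about 1 to 1.5%. It is modest in another respect: if the set of sizes becomes known, best-guess accuracy stays near 65%, so non-disclosure matters as much as the variation.

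The cost is one re-run of the list and re-filling of unused envelopes. The largest possible end-of-list difference between arms within a stratum rises from 5 to 6 (half of the largest block), so at worst from 20 to 24 over four strata. Sample size and analysis are unchanged.

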### Intervention

Following the initial assessment, participants in the intervention group will have an optometrist examination that will include measurement of objective refraction. These participants will then be prescribed a pair of single-lens distance glasses. For the estimated 80% of intervention participants who will not need an update of multifocal lens prescription (n = 234), the correction for the single-lens glasses will be matched with the prescription of the upper segment of their pre-trial multifocal glasses. For the expected 20% of participants (n = 56) who have had a significant change in distance correction since the most recent prescription [defined as a change of +/- 0.5 dioptres for refractive error (using the spherical equivalent: sphere + half cylinder), or more than 0.75 dioptres for astigmatism (measured in minus cylinders) and at least +0.50 dioptres change in the reading addition], updated multifocal lenses will be provided. The distance component of the updated multifocal correction will then be used for the prescription of new single-lens distance glasses, thereby making the transition between the two types of glasses easier.

At a second visit (approximately four weeks following the initial assessment) participants will be fitted with their glasses. An optometrist/counsellor will then demonstrate how multifocal glasses can impair the visual abilities required for detecting obstacles and judging depth. This will be achieved by administering the tests of distance edge contrast sensitivity and depth perception with participants viewing the visual stimuli through the upper and lower portion of their multifocal lenses and distance lenses [5]. The difference in upper and lower visual performance will be shown to the participant and the rationale for performing these tests will then be explained. Figure 2 shows the tests for measuring upper and lower lens contrast sensitivity used in the counselling (Figure 2).

**Figure 2 F2:**
[figure not shown]
**The distance contrast sensitivity tests**. Panel A shows a participant (with his chin placed on a comfortable chinrest to prevent head movement) viewing the test plate through the lower (reading) segments of his glasses. Panel B shows the participant looking directly at the test stimulus through the upper (distance) segments of his glasses. Any difference in contrast vision between the two conditions is then shown to the participant as part of the counselling session.

Participants will also be shown photographs of steps and streetscapes with and without simulated lower field blur to further reinforce why multifocal glasses may increase the risk of falls. Figure 3 shows the photographs of a simulated view of a street scene as viewed through single-lens distance (panel a) and bifocal glasses (panel b) (Figure 3). This counselling session will be conducted in line with the health belief model [20], and is considered crucial to convince older wearers of multifocal glasses that they are personally at risk of fall-related injuries and that the benefits of wearing single lens glasses outweighs the inconvenience of dealing with two pairs of glasses.

